## Abstract

**Background:**

United States military Veterans from recent conflicts are experiencing symptoms related to posttraumatic stress disorder (PTSD). Many Veterans are resistant to conventional health and mental health interventions (e.g., medication, psychotherapy). Alternative treatment approaches are needed. An underlying feature of PTSD is exaggerated inflammation, both peripherally and in the central nervous system. This inflammation is thought to play an important role in the vulnerability to, aggravation of, and persistence of PTSD symptoms. Therefore, an innovative intervention strategy would be the use of immunoregulatory/anti-inflammatory probiotics to reduce inflammation. Here we describe the rationale, design, and methods of a randomized placebo-controlled trial (RCT) of *Lactobacillus rhamnosus* GG (LGG; ATCC 53103) for posttraumatic stress disorder (PTSD).

**Methods:**

This is a Phase IIa trial of LGG for United States military Veterans with PTSD, using a longitudinal, double-blind, randomized placebo-controlled design. The primary outcome measure is plasma concentration of high-sensitivity C-reactive protein.

**Conclusion:**

Despite the fact that symptoms associated with PTSD can be disabling, individuals living with this trauma-related disorder have limited options in terms of evidence-based interventions. Recent research efforts aimed at highlighting the biological mechanisms of PTSD suggest that increased inflammation and altered autonomic nervous system activity may be treatment targets, and that immunoregulatory probiotics, such as LGG, have the potential to decrease trauma-induced inflammatory responses, as well as associated symptoms. This manuscript describes the best powered human subjects Phase IIa trial, to date, of a probiotic intervention for those living with PTSD.

## Introduction

1

Since October of 2001, approximately 2.7 million troops have been deployed in the recent conflicts, with many reporting mental health concerns upon return [1,2]. Posttraumatic stress disorder (PTSD), a trauma-related disorder that can result from exposure to an event that poses actual or threatened death or injury, has become increasingly prevalent. Although the estimated lifetime prevalence of PTSD in the United States (US) adult population is approximately 8.7% [3], findings suggest that approximately 20% of returning Service Members meet criteria for PTSD or associated mental health conditions [4]. Chronic PTSD symptoms associated with disruptions in the regulation of emotional and cognitive processes, including hypervigilance, low frustration tolerance/irritability, and impaired decision-making [5], can pose significant challenges for Service Members and Veterans*.* Thus, there is an ever-increasing need for the identification of new treatment options that are implementable, safe, and non-stigmatizing.

Treatment guidelines for PTSD commonly center around forms of psychotherapy, such as exposure-based or cognitive restructuring interventions [6]. However, traditional treatments can be ineffective, with non-response rates in outcome studies often reaching as high as 50% [7]. Further, many Operation Enduring Freedom/Operation Iraqi Freedom/Operation New Dawn (OEF/OIF/OND) Veterans can be resistant to engaging in conventional mental health treatments [8], highlighting the importance of exploring alternative interventions. Use of complementary and alternative medicine (CAM), particularly for symptoms associated with stress/trauma, has quickly risen in the US. Interestingly, research suggests that Veterans with PTSD may be more accepting of CAM approaches than those without this condition [9]. Taken together, these data indicate the need to explore novel CAM intervention strategies that can target mechanisms underlying PTSD symptomology.

Recent research efforts aimed at elucidating potential biological mechanisms of PTSD have facilitated the development of such novel interventions. Psychological trauma is known to be associated with altered autonomic nervous system activity [10] and impaired regulation of the hypothalamic–pituitary–adrenal (HPA) axis and insufficient glucocorticoid-signaling [11,12]. Evidence for inflammatory drivers of trauma-related disorders has also been accumulating [13,14]. For example, increased circulating levels of interleukin (IL)-6 immediately following trauma exposure have been found to predict the later development of PTSD symptoms [15]. Although not confirmed in all studies, low-grade inflammation has been shown to be associated with PTSD and physiological stress responses, as indicated by elevated serum C-reactive protein (CRP), IL-1β, IL-6, IL-12, interferon gamma (INFγ) and tumor necrosis factor (TNF) [[16], [17], [18], [19], [20], [21], [22], [23], [24]]. In prospective studies, high baseline plasma concentrations of CRP, measured pre-deployment among Military personnel, were associated with an increased likelihood of having PTSD symptoms post-deployment, suggesting that inflammation prior to trauma exposure may predispose individuals to developing a trauma-related condition [25]. In line with this finding, machine learning approaches have demonstrated that among features assessed prior to deployment, biomarkers of inflammation, including CRP, were among the highest-ranking features predicting PTSD symptoms following deployment [26]. Gene expression profiles of peripheral blood mononuclear cells (PBMCs) 1- and 4-months following trauma distinguish trauma survivors with PTSD from those without PTSD, signifying that altered immune functional status following trauma exposure is also predictive of PTSD [18]. Moreover, individuals with PTSD show enhanced spontaneous secretion of IL-1β, IL-6, and TNF from PBMCs, which correlate with symptom severity [18,27]. Anti-inflammatory interventions have been successfully used among those with other psychiatric disorders [[28], [29], [30], [31]]. Therefore, it is reasonable to suggest that anti-inflammatory or immunoregulatory agents may be a useful intervention for treating symptoms of PTSD.

The use of probiotics, or microorganisms deemed beneficial for human health, as a method for reducing inflammation has become a growing area of interest. *Lactobacillus rhamnosus* GG (LGG) is a gram-positive strain of the *Lactobacillus rhamnosus* species that is found in the human gut microbiome. LGG is immunoregulatory, increasing peripheral regulatory T cells (Treg) and anti-inflammatory cytokines including IL-10, and decreasing proinflammatory cytokines such as IL-6 [32,33]. It is one of the most widely used probiotic strains [34] and has been studied in relation to gastrointestinal health, stimulation of the immune response to improve vaccination efficacy, and prevention of allergic symptoms [[35], [36], [37], [38], [39]].

Accumulating evidence also suggests that probiotics with anti-inflammatory and immunoregulatory properties, such as LGG [32,33], have the potential to decrease trauma-induced inflammatory responses, while being highly accessible, low-cost, self-sustaining (e.g., portable) and, based on previous safety and tolerability trials, without significant side effects [40]. Moreover, in our recent pilot randomized placebo controlled trial among OEF/OIF Veterans with PTSD and mild traumatic brain injury (mTBI), supplementation with *Lactobacillus reuteri DSM 17938*, another probiotic with anti-inflammatory and immunoregulatory properties, was found to be feasible, acceptable, and safe [40], and was associated with decreases in plasma CRP that approached statistical significance, as well as decreases in an objective measure of distress (stress-induced increase in heart beats per minute [BPM]) during the Trier Social Stress Test) [40], a biomarker of autonomic stress responsivity [41,42].

Based on previous research [14,22,23,43], we created a working model of PTSD, with an emphasis on immunomodulatory factors (see Fig. 1). The presented clinical trial is based on our overarching theses that: 1) elevated inflammation increases risk of developing PTSD; 2) chronic inflammation and impaired immunomodulation perpetuate symptoms among those with PTSD; 3) exacerbation of inflammation is associated with increased severity of PTSD symptoms; and, 4) administration of an anti-inflammatory/immunoregulatory probiotic is likely to influence an individual's gut microbial community, and decrease intestinal permeability (IP) and systemic inflammation, as well as dampen autonomic responsivity and PTSD symptoms.

**Fig. 1 fig1:**
[figure not shown]
Working model of PTSD with an emphasis on immunomodulatory factors in the etiology and pathophysiology of PTSD. The model includes the influence of pre-existing factors that contribute to individual variability in physiological and psychological responses to trauma, leading to development and persistence of PTSD in a subset of individuals. Abbreviations: ANS, autonomic nervous system; HPA, hypothalamic-pituitary-adrenal; PTSD, posttraumatic stress disorder.

The goal of this Phase IIa placebo-controlled randomized controlled trial (ClinicalTrials.gov Identifier: NCT04150380) is to investigate the effects of daily oral administration of LGG (ATCC 53103) in a cohort of OEF/OIF/OND Veterans with PTSD as assessed by the gold standard Clinician Administered PTSD Scale-5 (CAPS-5) [44] who also have Functional Bowel Disorders (FBD), including irritable bowel syndrome. Outcomes include plasma concentration of high-sensitivity CRP (mechanistic, primary), and PTSD symptom severity (clinical, exploratory) [45]. Additional biological signatures will be considered exploratory. The primary hypothesis is that those who receive LGG supplementation will respond with lower plasma levels of CRP as compared to those allocated to a placebo supplement. Exploratory hypotheses include, as compared to those allocated to placebo, those who receive LGG supplementation will respond with: 1) decreased PTSD symptoms; 2) increased abundance of LGG and community-level shifts (e.g., increased alpha diversity) in the gut microbiota (measured using RT-qPCR and DNA sequencing of the 16S rRNA gene, respectively), decreases in IP (decreased fatty acid binding protein 2 [FABP2] and D-amino acid oxidase [DAO]), increases in plasma concentrations of anti-inflammatory biomarkers (IL-10, IL-4), decreases in additional plasma biomarkers of inflammation (IL-6, IL-8, IFNγ, IL-1α, IL-1β, and IL-12p70), reduced stress responsivity (biological and psychological) during and after participation in the Cyberball task, and improved decision-making (measured by performance on the modified Iowa Gambling Test [mIGT]); and, 3) the effect of LGG supplementation on stress responsivity, decision-making, and PTSD symptom severity will be mediated by effects of LGG supplementation on the gut microbiota, IP, and plasma biomarkers of inflammation.

## Materials and methods

2

### Study design

2.1

The described Phase IIa trial will examine the effects of supplementation with LGG, a probiotic with anti-inflammatory and immunoregulatory properties, using a longitudinal, double-blind, randomized placebo-controlled design. It is expected that up to 215 Veterans will participate in initial evaluation procedures, with 118 being randomized to one of two interventions (probiotic or placebo supplementation; see Consort Diagram, Fig. 2). Randomization will be stratified by sex. This study is being conducted according to the guidelines outlined in the Declaration of Helsinki and all procedures involving human participants were approved by the Colorado Multiple Institutional Review Board (COMIRB).

**Fig. 2 fig2:**
[figure not shown]
Consort diagram. Abbreviations: LGG, *Lactobacillus rhamnosus* GG.

At Time 1 (T1, Initial Study Assessment), diagnoses of PTSD and functional bowel disorder (FBD) will be confirmed. A blood draw will be conducted to identify an individual's baseline CRP level for inclusion, based on plasma CRP concentration >1.0 mg/L, the clinical threshold for average risk of cardiovascular disease [46]. Between Time 1 and Time 2 (T2, Assessment and Randomization Visit), participants will keep a pre-supplementation daily diary of gastrointestinal (GI) symptoms for approximately 2 weeks. At T2, data will bei collected regarding group profile/potential confounding variable measures, psychological outcomes, and biological signatures. Between T2 and Time 3 (T3, End of Study Period Assessment), individuals will supplement with LGG or placebo (for 8±2 weeks), and measures of tolerability, safety, acceptability, and feasibility will be collected. Data regarding diet, sleep, exercise, and PTSD symptoms will also be collected (via phone or email surveys). At T3, data will be collected regarding psychological outcomes (e.g., PTSD symptoms), and biological signatures (e.g., inflammation), as well as potential covariates (see Fig. 3, Participant Flow Diagram).

**Fig. 3 fig3:**
[figure not shown]
Participant flow diagram. Abbreviations: AACTG, Adult AIDS Clinical Trials Group; BEVQ, Beverage Intake Questionnaire (BEVQ-15); BMI, body mass index; CAPS-5, Clinician Administered PTSD Scale-5; COVID-19, Coronavirus Disease 2019; CRP, C-reactive protein; CTQ, Childhood Trauma Questionnaire; GASE, Generic Assessment of Side Effects; GASE-P, Generic Assessment of Side Effects – Probiotics; GI, gastrointestinal; IBS-SSS, Irritable Bowel Syndrome Severity Scoring System; IPAQ, International Physical Activity Questionnaire; ISI, Insomnia Severity Index; mIGT, Modified Iowa Gambling Task; MMIS, Modified Morisky Medication-Taking Adherence Scale; NHIS, National Health Interview Survey (NHIS) - Chronic Conditions; NIH, National Institutes of Health; OSU-TBI-ID, Ohio State University Traumatic Brain Injury (TBI) Identification Method; PCL-5, Posttraumatic Stress Disorder Checklist for DSM-5; PHQ-9, Patient Health Questionnaire-9; PSQI, Pittsburgh Sleep Quality Index; RAND-36, 36-Item Short Form Survey (SF-36) - RAND Corporation; ROME, Rome IV Diagnostic Questionnaire for the Adult Functional GI Disorders; SCID-5, Structured Clinical Interview for DSM-5-Research Version (SCID-5 for DSM-5, Research Version; SCID-5-RV, Version 1.0.0); T1, Time 1 assessment; T2, Time 2 assessment; T3, Time 3 assessment; TOMM, Test of Memory and Malingering; TSQM, Modified Treatment Satisfaction Questionnaire; UWRAP, University of Washington Risk Assessment Protocol-Revised.

### Probiotic and placebo interventions

2.2

LGG ATCC strain 53103 (Chr. Hansen A/S, 1.0 x 10^10^ colony-forming units (CFUs)/capsule) is being used in the proposed study. Participants will be randomized to one of two conditions in which they are instructed to consume one LGG or placebo supplementation capsule daily, for 8±2 weeks.

Through traditional and molecular methods, our team will conduct independent testing regarding the purity and viability of the probiotic upon receipt of the capsules and after the expected shelf life. After initial receipt, a randomized subsampling of 10 capsules (∼0.5%) will be analyzed, and another 10 pills will be stored in the lab under the same conditions as recommended to the participants in the study. An identical process will be conducted for placebo pills to verify absence of LGG. The viability and CFUs of the probiotic and placebo will be confirmed against the manufacturer's documentation by culturing on *Lactobacillus* selection agar plates. Furthermore, the purity and quantity of the probiotic will be confirmed against the manufacturer's documentation by reverse transcription quantitative polymerase chain reaction (RT-qPCR).

### Study population

2.3

Potential participants will be willing and eligible US military Veterans between the ages of 18 and 60 from the following populations: 1) those seeking outpatient mental health, rehabilitative, psychological, or other services within a VA Health Care System; 2) those in existing clinical and research databases; and 3) Veterans in the community not seeking care at the VA. Inclusion and exclusion criteria are presented in Table 1.

**Table 1 tbl1:** Inclusion and exclusion criteria.

**Inclusion criteria**
History of at least one deployment in support of Operation Enduring Freedom/Operation Iraqi Freedom/Operation New Dawn (OEF/OIF/OND)
Current diagnosis of PTSD per the Clinician Administered PTSD Scale-5 (CAPS-5)
Current diagnosis of a Functional Bowel Disorder including Irritable Bowel Syndrome [IBS]) by the ROME IV
CRP level of 1.0 mg/L or above at Time 1
Medical clearance to participate by study providers
Age between 18 and 60
Ability to provide informed consent
Willingness to abstain from probiotic supplements (pills, tablets, oils, foods, etc.) other than the investigational product provided until all study procedures are completed
Willingness to provide blood and stool samples
**Exclusion criteria**
Inability to adequately respond to questions regarding the informed consent procedure
Currently involved in the criminal justice system as a prisoner or ward of the state
Non-English speaking
Current (past month) alcohol or substance abuse or dependence, excluding marijuana
Lifetime history of bipolar disorder or psychosis or anxiety disorders
Consistent (e.g., 5x/week or greater) probiotic supplementation within the last month, including probiotic food products such as yogurt, as determined by phone screen interview and Probiotic Food Check List
Receiving intravenous, intramuscular, systemic or oral antibiotics within the last month
Presence of central venous catheters (CVCs)
Gastrointestinal (GI) barriers as identified by the 2-week run-in period as determined by the study team
Participation in conflicting interventional research protocol
Vital signs outside of acceptable range, i.e., blood pressure >160/100, pulse >100
Use of any of the following drugs within the last 6 months: antifungals, antivirals or antiparasitics (intravenous, intramuscular, or oral); oral, intravenous, intramuscular, or inhaled corticosteroids; cytokines or cytokine inhibitors; methotrexate or immunosuppressive cytotoxic agents
Acute disease at the time of enrollment (defer sampling until the participant recovers). Acute disease is defined as the presence of a moderate or severe illness with or without fever (e.g., oral temperature >100 °F)
Any medical condition deemed exclusionary by the Principal Investigators
History of cancer
Unstable dietary history as determined by the PIs (e.g., major changes in diet during the previous month, where the subject has eliminated or significantly increased a major food group in the diet)
Positive test for human immunodeficiency virus (HIV), Hepatitis B virus, or Hepatitis C virus
Any confirmed or suspected condition/state of immunosuppression or immunodeficiency (primary or acquired) including HIV infection, or those receiving immunosuppressive drugs or treatment including antineoplastic therapy, post-transplantation immunosuppressive therapy, and/or radiation therapy
Major surgery of the GI tract, with the exception of cholecystectomy and appendectomy, in the past five years. Any major bowel resection at any time
Female who is pregnant or lactating
Treatment for or suspicion of ever having had toxic shock syndrome
History of moderate and/or severe traumatic brain injury

### Measures and variable definitions

2.4

For a full list of measures and variable definitions, see Table 2.

**Table 2 tbl2:** Study measures/outcomes and variable definitions.

Measure	Condition(s)/Factor(s) of Interest
Adult AIDS Clinical Trials Group (AACTG)	Supplement adherence
Beverage Intake Questionnaire (BEVQ-15)	Frequency/quantity of intake of beverages
Bristol Stool Scale	Number of daily bowel movements and consistency of stool
C-reactive protein (CRP)^a^	Inflammation
Clinician Administered PTSD Scale-5 (CAPS-5)	Current PTSD diagnosis
Childhood Trauma Questionnaire (CTQ)	Childhood abuse experiences
COVID-19 Questionnaire	Impact of COVID-19 pandemic and stressors related to the pandemic
Credibility Scale	Sense of supplementation credibility
D-amino acid oxidase (DAO)^b^	Intestinal permeability
Expectancy Scale	Expectations regarding supplementation
Fatty acid binding protein 2 (FABP2)^b^	Intestinal permeability
Generic Assessment of Side Effects (GASE)	Medication side effects
Generic Assessment of Side Effects – Probiotics (GASE-P)	Supplement side effects
Heart rate variability (HRV)	Physiological stress
Height and weight	Body Mass Index (BMI)
Interleukin (IL)-6, interferon gamma (IFNγ), tumor necrosis factor (TNF), IL-1α, IL-1β, IL-12p70, IL-8, IL-4, and IL-10^b^	Inflammation
Insomnia Severity Index (ISI)	Insomnia symptom severity
International Physical Activity Questionnaire (IPAQ)	Physical activity
Irritable Bowel Syndrome Severity Scoring System (IBS-SSS)	Severity and frequency of abdominal pain and abdominal distension, dissatisfaction with bowel habits, and interference with quality of life
Medications Log	Current medications and dosage
Modified Iowa Gambling Task (mIGT)	Decision making
Modified Morisky Medication-Taking Adherence Scale (MMAS)	Supplement adherence
Modified Treatment Satisfaction Questionnaire (TSQM v1.4)	Supplement side effects
National Health Interview Survey (NHIS) - Chronic Conditions	Chronic health symptoms
National Institutes of Health Daily Food List	Food intake
Ohio State University Traumatic Brain Injury (TBI) Identification Method (OSU TBI-ID)	Lifetime history of TBI
Patient Health Questionnaire-9	Depression symptom severity
Pittsburgh Sleep Quality Index	Subjective sleep duration
Posttraumatic Stress Disorder Checklist for DSM-5 (PCL-5)^b^	PTSD symptom severity
Probiotic Food Check List	Consumption of probiotic-containing food products
Psychological Stress Measure (PSM)^b^	Perceived stress
Rocky Mountain MIRECC Demographic Form	Demographics
Rome IV Diagnostic Questionnaire for the Adult Functional GI Disorders	Digestive system disorders
Structured Clinical Interview for DSM-5-Research Version (SCID-5 for DSM-5, Research Version; SCID-5-RV, Version 1.0.0)	Axis I psychiatric disorders
Supplement Usage Log	Date, time, and amount of each probiotic dose
Test of Memory and Malingering (TOMM)	Memory
University of Washington Risk Assessment Protocol-Revised (UWRAP)	Risk assessment
Veterans RAND 36, 36-Item Short Form Survey (SF-36) - RAND Corporation	Health-related quality of life
Visual Analog Scale (VAS)^b^	Perceived stress

a Primary outcome.

b Additional outcomes measures.

### Outcome measures

2.5

The primary mechanistic outcome for this study is plasma concentration of high-sensitivity CRP. Exploratory outcomes include: 1) PTSD symptom severity (PTSD Symptom Checklist for DSM-5; PCL-5) [47]; 2) type and abundance of LGG and community-level gut microbiota (measured using qRT-PCR and DNA sequencing of the 16S rRNA gene); 3) IP (FABP2 and DAO; 4) plasma concentrations of IL-10, IL-4, IL-6, IL-8, IFNγ, IL-1α, IL-1β, and IL-12; 5); biological and psychological stress responsivity during and after participation in the Cyberball task [48]; and, 6) decision-making (mIGT). All outcomes are listed in Table 2.

### Safety monitoring

2.6

Adverse Events from the Study Drug. Participants will be asked about GI symptoms throughout the study as identified in procedures. Participants will be asked about new symptoms, adverse events and any new medications or supplements during the weekly check-in phone call using the Generic Assessment of Side Effects (GASE)/Generic Assessment of Side Effects – Probiotics (GASE-P).

Suicide Risk Assessment and Management. All research staff will also complete Veterans Affairs (VA) required research trainings. Study staff will contact the PI or her clinical designee if other concerning information regarding the participant's safety or the safety of others is identified during administration of the protocol. Assessors will have emergency contact information available at all times for the PI or designee, as well as crisis management and emergency services (e.g., VA National Veterans Crisis Line, Psychiatric Emergency Services, 911). If contacted, the PI or her clinical designee will conduct a more thorough risk evaluation and will initiate appropriate follow-up procedures.

For assessments conducted over the phone, when indicated, assessors will stay on the telephone with the participant until they are able to consult with the PI or clinical designee, determine next steps, and follow through with them. Prior to beginning the phone assessment, assessors will ask participants to provide the address of the location they are at while completing the phone assessment so that the assessor, after consulting with the PI or designated clinician, can direct emergency services to the participant's location when warranted. With respect to confidentiality, prior to participating in the study, informed consent documents will contain statements explaining mandatory reporting requirements for information regarding intention to harm self or others. In situations where confidentiality is breached due to threats to participants' or others' safety (e.g., suicide or homicide risk), precautions will be taken to protect their privacy by limiting the information being disclosed to only the minimum information necessary to ensure the safety and welfare of participants and others affected.

Adverse Events. Significant adverse events are not expected. For this study, adverse events are defined as symptoms reported by the participant that are directly related to participation in the study. The study PIs will be notified of any complaints or reports of adverse events. Data and safety monitoring will be regularly reviewed by the study personnel and the Study PIs to ensure protocol adherence and participant safety. Any unexpected serious adverse events (uSAEs), defined as death, life threatening illness, suicide attempt, hospitalization or prolonged hospitalization, and persistent/significant disability, will be reported to COMIRB by the study PIs within 5 days of them being made aware. Other adverse events will be recorded and reported at continuing review. In addition, there is a Data Safety Monitor Board (DSMB) who will review data produced by the study team and will meet with the lead investigators and study statistician on a regular basis.

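### The adverse event definition requires relatedness and participant report, so the safety comparison between arms is filtered by attribution, and it conflicts with the serious-event list beside it

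*Protocol article*

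**What the plan says.** All the relevant text is in section 2.6, Safety monitoring, of the protocol article.

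- **General definition.** In this trial, "adverse events are defined as symptoms reported by the participant that are directly related to participation in the study".
- **Serious events.** The class is given as follows: "Any unexpected serious adverse events (uSAEs), defined as death, life threatening illness, suicide attempt, hospitalization or prolonged hospitalization, and persistent/significant disability". The stated duty is that such events "will be reported to COMIRB by the study PIs within 5 days of them being made aware". This clause has no relatedness wording.
- **Everything else.** "Other adverse events will be recorded and reported at continuing review".
- **Collection.** "Participants will be asked about new symptoms, adverse events and any new medications or supplements during the weekly check-in phone call", with the GASE and GASE-P side-effect instruments. Also, "Participants will be asked about GI symptoms throughout the study as identified in procedures". Neither sentence is limited to related symptoms.
- **Oversight.** "The study PIs will be notified of any complaints or reports of adverse events". A data safety monitoring board reviews what the study team supplies and meets regularly with the lead investigators and the statistician.

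Section 2.1, Study design, describes the trial as double-blind, randomised and placebo-controlled.

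**The concern.** A placebo-controlled, double-blind trial has one great advantage for safety: nobody has to decide case by case what caused an event. If all events are counted in both arms, the comparison itself shows whether the product causes harm. A definition that requires relatedness before an event counts puts individual judgement in front of that comparison.

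The events most likely to be lost are the ones that matter most. A known side effect is readily called related. A harm that nobody suspects is the least likely to be called directly related, and the section itself says that no significant adverse events are expected. The product is a live organism given to people with functional bowel disorders, where new symptoms can easily be put down to the underlying condition.

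The restriction to symptoms reported by participants is a second filter, independent of cause. It leaves out whatever staff observe or measure that the participant does not report as a symptom.

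**Working it through.** The article gives no figure on this point to reproduce: it states no adverse event rate and no share of events expected to be judged related. The check is to follow different kinds of event through the text of Safety monitoring.

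| Event | Meets the general definition? | Stated route |
|---|---|---|
| Non-serious symptom, reported, judged related | Yes | Recorded, continuing review |
| Non-serious symptom, reported on a weekly call, judged unrelated | No | Asked about, but no stated duty to record or report it as an adverse event |
| Sign observed or measured by staff, not reported as a symptom | No, whatever its cause | None stated under the adverse event heading |
| Unexpected hospitalisation or suicide attempt, judged unrelated | No, because of the relatedness condition | On the serious list by name, ethics committee within 5 days; unclear whether relatedness carries over |
| Unexpected death | No, since a death is not a symptom reported by the participant | On the serious list |
| Serious event regarded as expected | Only if it is a reported symptom judged related | Falls to the category of other adverse events, where the general definition applies |

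Three things follow.

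1. **The general definition and the serious list do not fit together.** Unexpected serious events are named as a kind of adverse event, yet death and hospitalisation are outcomes and not symptoms reported by a participant. Either the list overrides the general definition, or the definition narrows the list. The text does not say which.

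2. **The general definition and the weekly questions do not fit together.** The call asks about new symptoms and about adverse events as separate items. New symptoms are therefore wider than adverse events. The only stated duty to record and report non-serious events uses the narrower term.

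3. **The direction of the effect on the comparison is clear, although its size is not.** Let the true risks of an event be p1 (LGG) and p0 (placebo), and let a share s of events be judged related, equal in both arms because of blinding. The recorded risks are s × p1 and s × p0, and the recorded difference is s × p1 − s × p0 = s × (p1 − p0). For any s below 1 the recorded difference is smaller than the true one, and fewer events are available to detect it. Blinding makes s less likely to differ between arms; it does not bring s back to 1. An unsuspected harm is where s is likely to be lowest. The article gives no value for s, p1 or p0, so no numerical loss is claimed.

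**The case against.** The strongest reply is that little is really lost. Three parts of it stand.

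- **Serious events.** A reader might infer that serious events judged unrelated simply drop out. The document does not support this. Unexpected serious events, including hospitalisation and suicide attempt, are defined by outcome and have their own 5-day route, with no relatedness condition in that clause. What remains is ambiguity: whether the general definition carries over, and what happens to serious events regarded as expected.
- **Raw symptom data.** A reader might also infer that the trial could not show an unexpected harm at all. That goes too far. Weekly calls ask about new symptoms and new medications whatever their cause, gastrointestinal symptoms are followed throughout, and Table 2 adds the treatment satisfaction questionnaire, the medications log, the Bristol Stool Scale, the IBS severity score and a risk assessment. Symptoms judged unrelated are left out of the adverse event category but not necessarily out of the data.
- **The monitoring board.** Nothing in the article limits the board to events that meet the definition. What it receives would normally be set out in the full protocol or a charter, which are not shown.

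The reply does not rescue the definition. It is presented as the operative one for this study, so a fuller document could help only by contradicting it. Collecting symptoms on a call is not the same as recording and reporting them as adverse events, and signs observed or measured by staff are not covered by questions put to participants.

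**Conclusion.** The point holds, as one that should be fixed. The stated definition builds relatedness and participant report into what counts as an adverse event. Followed literally, it gives an adverse event table filtered by attribution, which may obscure an unexpected harm. It also contradicts the outcome-based serious-event list and sits badly with the unrestricted weekly questions.

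The conclusion rests on a literal reading of the definition and of the sentence on recording other adverse events. Staff may in practice record more than the wording requires. The number of events affected is unknown. The primary CRP analysis is unaffected, and double blinding makes a filter that favours one arm less likely.

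**What to change.** Reconcile the sentences in Safety monitoring as follows.

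1. Define an adverse event as any untoward medical occurrence from the first study procedure onward, whether or not considered related, and whether reported, observed or measured. Starting at the first procedure covers the T1 blood draw and the run-in of about two weeks.
2. Record relatedness and expectedness as separate fields, assessed under blinding.
3. State that serious events are captured regardless of judged cause, and say how serious events regarded as expected are handled.
4. Tabulate all events and all serious events by arm for the monitoring board and the final report, with related events as a subset.

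The cost is moderate. More events must be logged. The article describes a trial already under way, so the change needs an approved amendment, and weekly-call data already collected must be re-coded so that the whole trial follows one definition. The weekly calls already ask about new symptoms and medications, so no new contact with participants is required for that part.
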